### Contraceptive Prevalence

Using modern contraceptive prevalence estimates for Lilongwe from the 2010 Malawi DHS, we expect a modern contraceptive prevalence rate of 19.5% among women aged 18 to 35 years who are either currently pregnant or who are up to 6 months postpartum at baseline. To infer a potential effect size for our intervention, we look to evidence from (1) the Navrongo study in Ghana, which found that a family planning intervention with a comprehensive outreach and contraceptive delivery component increased contraceptive use by 6 to 8 percentage points over a 4-year study period and (2) the Matlab study in Bangladesh, which found far larger effects of contraceptive uptake among women in the intervention areas over a longer study period [9,23]. Our power calculations show that we will have 90% power to detect a 6.5 percentage point increase in the modern contraceptive prevalence rate in the intervention arm, from 19.5% to 26%, assuming that we will have an attrition-adjusted sample of 1460 women (730 women in each arm) at the end line.

Table 3 presents the levels of power 1-ß that will be achieved for various minimum effect sizes for modern contraceptive prevalence use (ie, the difference in the modern contraceptive prevalence rate between the intervention and control arms at end line), assuming a baseline contraceptive prevalence rate of 19.5 percentage points in both intervention and control arms and a fixed end-line sample size of 1460 women (730 in each arm).

**Table 3 table3:** Power calculations—contraceptive prevalence rate.

Control CPR^a^, n (%)	Intervention CPR, n (%)	Significance level, α	Control sample size	Intervention sample size	Power
142 (19.5)	190 (26)	.05	730	730	0.90
142 (19.5)	183 (25)	.05	730	730	0.79
142 (19.5)	175 (24)	.05	730	730	0.65
142 (19.5)	168 (23)	.05	730	730	0.47

^a^CPR: contraceptive prevalence rate.

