### Study Setting

Our study was conducted in urban Lilongwe, the capital of Malawi. Despite declining birth rates and improvements to maternal health care, the total fertility rate or the average number of births per woman has remained relatively high in Malawi. In 2017, the average total fertility rate in Malawi was 4.2 births per woman (with a slightly lower fertility rate in Lilongwe), which is below the average total fertility rate of 4.9 births per woman in sub-Saharan Africa, but almost twice the average total fertility rate of 2.7 births per woman in South Asia and more than twice the average total fertility rate of 2.2 births per woman in Latin America and the Caribbean [16,17]. In addition, estimates from the 2015-16 Malawi Demographics and Health Survey (MDHS) show that the contraceptive prevalence rate in Malawi was 45.2% among all women of reproductive age (15-49 years) and 59.2% among married women of reproductive age. These estimated contraceptive prevalence rates are a significant increase from the 32.6% and 46.1% prevalence rates for all women and married women, respectively, from the 2010 MDHS. Nevertheless, the unmet need for family planning has remained high, with an estimated 18.7% of women in Malawi reporting to have an unmet need for spacing or limiting births [17]. Injectable contraceptives were reported to be the most popular method in Malawi in 2010 and were used by 22.5% of women, followed by intrauterine devices (IUDs) and female sterilization at 9% and 8.3%, respectively [17]. The method mix of women has not changed significantly over time among married women in Malawi, as injectable contraceptives, IUDs, and female sterilization remain to be the most popular methods among married women and are used by 30%, 11.5%, and 10.9%, respectively [17].

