### Analysis Plan

Analysis of quantitative study data will be conducted using STATA and R (the R Project), where appropriate. A descriptive analysis will be performed for all variables, and unadjusted comparisons between experimental arms will be conducted. Descriptive statistics will be performed, including frequencies, means, and standard deviations. In addition, chi-square tests and one-tailed *t* tests will be used to examine associations in the data. A *P* value <.05 will be considered statistically significant for all statistical tests that are conducted. Given our hypotheses of the impact of our intervention on our key outcomes, one-sided hypotheses tests will be conducted for all our main analyses. Continuous variables will be tested for normality and nonnormal values will be categorized or transformed appropriately.

Our main econometric specifications will estimate the intent-to-treat (ITT) effect of our family planning intervention on fertility and other outcomes by directly regressing our outcomes of interest on a binary variable indicating receipt of the intervention. The main econometric specification for estimating the ITT effect of our family planning intervention is defined as follows:

where *Y_it_* is the outcome variable of interest for woman *i* in the period *t*=0,1,2 for baseline, 1-year follow-up, and 2-year follow-up, respectively; *T_it_* is an indicator of assignment to the treatment arm; *X_it_* is a vector of individual-level covariates that are controlled for in the analysis; *_i_* is the individual-specific fixed effect; *Y_i0_* is the baseline level of the outcome; and *ε_it_* is the error term. Here, the outcome variables of interest include immediate, intermediate, and long-term outcomes mentioned in the previous sections.

We will conduct several subgroup analyses to examine how the family planning intervention effects vary across particular subpopulations. Subgroups of interest include pregnant women, new mothers, women who have previously used family planning, women who expressed a desire to space or limit births at baseline, poorer women, and women with low educational attainment. In addition, we will estimate heterogeneous treatment effects for girls, older children, and high-parity households.

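### Table 3 uses the contraceptive prevalence of pregnant and early-postpartum women (19.5%) as the control rate two years later; at the article's married-women rates, the stated 90% power for 6.5 points becomes about 80%

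*Protocol article*

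**What the plan says.** All references are to the protocol article.

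- **Contraceptive Prevalence** derives a starting rate of 19.5% for modern methods from the 2010 national survey. It is the rate expected "among women aged 18 to 35 years who are either currently pregnant or who are up to 6 months postpartum at baseline".
- The same section defines the effect in Table 3 as "the difference in the modern contraceptive prevalence rate between the intervention and control arms at end line". Every row of the table nevertheless has 19.5% as the control rate, "assuming a baseline contraceptive prevalence rate of 19.5 percentage points in both intervention and control arms and a fixed end-line sample size" of 730 per arm. Only the intervention rate varies (26%, 25%, 24%, 23%).
- The resulting claim is "90% power to detect a 6.5 percentage point increase in the modern contraceptive prevalence rate in the intervention arm, from 19.5% to 26" per cent. The effect size leans on a cited study that "increased contraceptive use by 6 to 8 percentage points over a 4-year study period".
- **Study Setting** gives contraceptive prevalence for Malawi as 46.1% of married women in 2010 and "59.2% among married women of reproductive age" in 2015-16. For all women the figures are 32.6% and 45.2%.
- **Analysis Plan** sets the threshold: "A *P* value <.05 will be considered statistically significant for all statistical tests that are conducted". It makes the main analyses one-sided.
- **Sample Size and Power Calculations** names contraceptive prevalence as one of two key outcomes the trial is powered for, although fertility is called the primary basis.

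**The concern.** The 19.5% describes a passing state. Eligibility required a woman to be pregnant or to have given birth within 6 months of the baseline screening. Pregnant women have little reason to be using a method, and many others have only just delivered. Two years later, a woman without a further pregnancy is about 15 to 30 months postpartum (24 − 9 to 24 + 6). The control rate can be expected to move even if the intervention does nothing. The calculation neither projects that movement nor shows how power depends on it.

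The variance of a proportion, p(1 − p), is 0.157 at 19.5%, 0.248 at 46.1% and 0.242 at 59.2%, so it is 1.5 to 1.6 times as large at the married-women rates. The same absolute difference is then harder to detect. What is at stake is an explicit 90% figure for a primary outcome, which readers would use to interpret a null or borderline result.

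**Working it through.** **Inputs.** Control rate 19.5%, difference 6.5 points and 730 per arm (Contraceptive Prevalence, Table 3); α = .05, one-sided (Analysis Plan); alternative control rates 46.1% and 59.2% (Study Setting), used as an assumption.

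**Formula.** Two-proportion z-test with pooled null variance and continuity correction:

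power = Φ[(d − c − 1.645·SE0) / SE1], where
- d = p2 − p1
- c = 0.5(1/n1 + 1/n2)
- SE0 = √[p̄(1 − p̄)(1/n1 + 1/n2)], with p̄ the sample-size-weighted mean of p1 and p2
- SE1 = √[p1(1 − p1)/n1 + p2(1 − p2)/n2]

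**Step 1: reproduce Table 3.** For 19.5% vs 26%: c = 0.00137, SE0 = 0.02194, SE1 = 0.02188, so (0.065 − 0.00137 − 0.03609)/0.02188 = 1.259 and power = 0.896.

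| Intervention rate | Table 3 | One-sided, corrected | One-sided, uncorrected |
|---|---|---|---|
| 26% | 0.90 | 0.896 | 0.907 |
| 25% | 0.79 | 0.794 | 0.811 |
| 24% | 0.65 | 0.647 | 0.670 |
| 23% | 0.47 | 0.470 | 0.496 |

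The corrected one-sided test matches all four rows. A two-sided test does not (0.827 in the first row with correction, 0.843 without).

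**Step 2: change only the control rate.** Same 6.5 points, 730 per arm.

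- 46.1% vs 52.6%: SE0 = 0.02617, SE1 = 0.02611; (0.065 − 0.00137 − 0.04304)/0.02611 = 0.788; power 0.785 (0.800 uncorrected).
- 59.2% vs 65.7%: SE0 = 0.02535, SE1 = 0.02529; (0.065 − 0.00137 − 0.04169)/0.02529 = 0.867; power 0.807 (0.822 uncorrected).

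**Step 3: the same for the women retained.** Follow-Up Surveys reports 1669 women reinterviewed at year 2. If loss was proportional to the randomised numbers (an assumption), that is 1669 × 1117/2143 = 870 control and 1669 × 1026/2143 = 799 intervention women.

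One-sided, corrected results over a range of control rates (the detectable difference is the d that gives power 0.90):

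| Control rate at year 2 | Power for 6.5 points, 730/730 | Detectable difference (points) | Power for 6.5 points, 870/799 | Detectable difference (points) |
|---|---|---|---|---|
| 19.5% (as planned) | 0.896 | 6.6 | 0.929 | 6.1 |
| 30% | 0.826 | 7.4 | 0.869 | 6.9 |
| 40% | 0.791 | 7.7 | 0.838 | 7.2 |
| 46.1% | 0.785 | 7.8 | 0.832 | 7.3 |
| 50% | 0.786 | 7.8 | 0.833 | 7.3 |
| 59.2% | 0.807 | 7.5 | 0.852 | 7.05 |
| 70% | 0.865 | 6.9 | 0.903 | 6.5 |
| 75% | 0.904 | 6.5 | 0.935 | 6.1 |

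At 730 per arm, power returns to 0.90 at a control rate of about 74.5% (73% without correction). An 8-point difference at 730 per arm has power 0.914 at 46.1% and 0.930 at 59.2%.

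**The case against.** **The assumption is disclosed and the sum is right.** Both are true. Table 3 states its 19.5%, and all four rows reproduce, so this is not an arithmetic error. Disclosure does not make a baseline-state rate suitable for an end-line comparison, however.

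**The replacement rates are borrowed.** This stands as a limit on the size of the point. The 46.1% and 59.2% figures are national, cover married women of reproductive age, and are not labelled as modern methods only. The 19.5% concerns modern methods in Lilongwe at ages 18 to 35. The true year-2 rate in this cohort may differ from both.

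**A reader might infer that 90% power fails at every plausible end-line rate.** The documents do not support that. They give no end-line rate for these women. Power recovers at control rates above about 73% to 75% at the planned size, and at about 70% with the women retained. What can be said is that, at 730 per arm, the 90% claim fails at every other prevalence the article prints for Malawi: 32.6% (0.814), 45.2% (0.785), 46.1% and 59.2%.

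**A reader might also quote two-sided power, near 70%.** That mixes in a separate question. The plan specifies one-sided tests and Table 3 is one-sided, so the loss should be measured on that test.

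**The main model may be more efficient.** The Analysis Plan indexes both follow-ups and includes covariates and the baseline outcome, which could recover some power. Table 3 claims nothing from this: it is a simple end-line comparison of two proportions, and its figure has to stand on that basis.

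**Conclusion.** The concern holds as a planning-assumption error of moderate weight. The control-rate input describes women at baseline, while the comparison is made two years later. Under the assumption that the control rate lies between the article's two married-women figures, the chance of missing a true 6.5-point effect at 730 per arm roughly doubles, from about 10% to about 20%. Better retention than planned (1669 against 1460) narrows the gap but does not close it over that range.

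The trial is not shown to be too small. About 80% power remains for 6.5 points at the planned size, and the effect detectable with 90% power stays within the range the plan cites. These sizes rest on the assumed control rates, proportional loss by arm for the retained sample, and the unadjusted one-sided test that reproduces Table 3.

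**What to change.** In Contraceptive Prevalence, replace the fixed 19.5% control rate with an expected year-2 control rate. Show it over a range, for example 30% to 60%, labelled as an assumption because no end-line rate is available for this cohort. Keep the planned one-sided test and name the method, including the continuity correction. Reword the 90% sentence to match: for 6.5 points at 730 per arm, power over that range is about 0.79 to 0.83. Add the difference detectable with 90% power for the retained sample, about 6.9 to 7.3 points over the same range under proportional loss, or recalculated from the actual numbers by arm.

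The cost is one table and one or two sentences, and a less favourable stated power. The sample size, outcome definition and analysis are unchanged.

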### Fertility (Number of Children Per Woman)

Similarly, we use fertility estimates for Lilongwe from the 2010 Malawi DHS and assume a baseline fertility rate of 4.5 births per woman in the sample at baseline. To infer a potential effect size, we again look to evidence from the Navrongo and Matlab studies, both of which found a total reduction of 1 birth per woman (equivalent to a 15% decrease in their respective baseline fertility) among women in their respective intervention arms over their respective study periods [9,23]. In recognizing that both the Matlab and Navrongo studies were larger-scale, cluster-randomized designs with longer follow-up periods, we estimate that we will only be able to observe differences of 0.5 births. Our power calculations show that we will have 99% power to detect a 0.5 birth per woman decrease, equivalent to a 12% decrease in fertility, in the intervention arm from 4.5 children per woman to 4.0 children per woman, assuming an attrition-adjusted sample of 1460 women (730 women in each arm) by end line.

Table 4 presents the levels of power 1-ß that will be achieved for various minimum effect sizes for fertility (ie, the difference in the average number of children per woman between the intervention and control arms at end line), assuming a baseline fertility of 4.5 children per woman in both intervention and control arms, a standard deviation of 2 children per woman for both arms, and a fixed end-line sample size of 1460 women (730 in each arm).

Finally, robustness checks (5% and 10% sample truncations and coarsening of independent variables) and falsification tests, which include placebo regression, simulation, and resampling methods, will be conducted to ascertain the strength and significance of our estimates. We will also conduct attrition-adjusted analyses to assess the extent of differential loss-to-follow-up outcomes.

**Table 4 table4:** Power calculations—fertility.

Control fertility, number of children per woman	Intervention fertility, number of children per woman	Significance level, α	Control sample size	Intervention sample size	Power
4.5	3.5	.05	730	730	1
4.5	4.0	.05	730	730	0.99
4.5	4.2	.05	730	730	0.89
4.5	4.3	.05	730	730	0.61

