### Sample Size and Power Calculations

The sample size of this study was powered to primarily identify the effect of using family planning on fertility; however, we will also examine the effects of the intervention on other maternal and child health outcomes of interest, in addition to key social and economic measures of well-being. On the basis of the preliminary power calculations for our primary outcomes of interest, a total of 2000 women were needed to be enrolled in the study. Of the women who were enrolled, the family planning intervention, baseline survey, and 2 follow-up surveys were administered to 1000 women (the treatment group), whereas a basic family planning information package, the baseline survey, and 2 follow-up surveys were administered to the other 1000 women (the control group).

Our target baseline sample consists of 2000 women who met the eligibility criteria and who consented to participate in the study. Previous research studies in Accra, Ghana, have found that 32% of initially screened women either did not meet the eligibility criteria or refused to participate [20-22]. Therefore, to meet our target sample size of 2000, we would need to screen 3000 households if we conservatively assumed a combined ineligibility or refusal rate of 32% from the screening. Of the 2000 women who were to be recruited into the study at baseline following the initial screening process, 1000 women were to be randomly assigned to the intervention arm and the remaining 1000 women were to be randomly assigned to the control arm. On the basis of prior study findings from Zambia [13], we expected an attrition rate of 27% in the sample over a 2-year study period, which would leave us with an attrition-adjusted sample size of 730 women in each treatment arm, or 1460 women overall, at the end of the 2-year study period.

Given this attrition-adjusted sample size, we have powered our study to detect effects in 2 key outcomes, namely changes in contraceptive prevalence and fertility, the latter measured by the number of births per woman.

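### The fertility power statement (99% for 0.5 fewer births per woman) is correct for its inputs, but its effect sizes and SD are on the wrong scale for births over a 2-year follow-up

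*Protocol article*

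**What the plan says.** Sample Size and Power Calculations in the protocol article gives fertility first place: "The sample size of this study was powered to primarily identify the effect of using family planning on fertility". The fertility subsection draws on the 2010 Malawi DHS to "assume a baseline fertility rate of 4.5 births per woman in the sample at baseline". It notes that two earlier studies found 1 fewer birth per woman. Because those studies were larger, cluster-randomised and followed for longer, it halves the effect: "we estimate that we will only be able to observe differences of 0.5 births". With "a standard deviation of 2 children per woman for both arms" and 730 women per arm after attrition, it concludes that "we will have 99% power to detect a 0.5 birth per woman decrease, equivalent to a 12% decrease in fertility". Table 4 lists power of 1, 0.99, 0.89 and 0.61 for end-line differences of 1.0, 0.5, 0.3 and 0.2 children per woman.

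The companion calculation under Contraceptive Prevalence states that "we will have 90% power to detect a 6.5 percentage point increase in the modern contraceptive prevalence rate", for the same women over the same period. The women are aged 18 to 35, pregnant or within 6 months of a birth at baseline, and followed for 2 years. The Analysis Plan specifies one-sided tests at .05 for the main analyses.

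**The concern.** Children born before randomisation cannot be affected by the intervention, and women pregnant at baseline deliver that child in either arm. Any difference between arms at end line must come from later births, and 2 years leaves room for few of them. An effect of 0.5 births taken off a level of 4.5 looks modest, but it has to come entirely out of those later births. The SD of 2 likewise describes spread in the total number of children, not in births during follow-up.

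Fertility is the outcome for which the sample size was primarily set, and the analysis was still under way when the article was written. A reader who takes 99% power at face value could treat a null fertility result as strong evidence of no effect, when the tabulated effect was never realistically within reach.

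**Working it through.** **1. Reproduce Table 4.** Inputs from the fertility subsection: n = 730 per arm, SD = 2, alpha = .05. The standard error of the difference is 2 × √(2/730) = 0.1047. Power = Φ(d/0.1047 − z), with z = 1.645 one-sided or 1.960 two-sided.

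| Difference d | Stated | One-sided | Two-sided |
|---|---|---|---|
| 1.0 | 1 | 1.000 | 1.000 |
| 0.5 | 0.99 | 0.999 | 0.998 |
| 0.3 | 0.89 | 0.889 | 0.818 |
| 0.2 | 0.61 | 0.605 | 0.480 |

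All four rows match one-sided. The 4.5 cancels in a difference of means, so the power depends only on the difference and the SD.

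**2. Births available in 2 years.** The documents give no expected number of new births over follow-up, so I derive a range from 4.5.
- Extreme case, all 4.5 births between ages 18 and 35: 2 × 4.5/18 = 0.50, or 2 × 4.5/17 = 0.53.
- Spread over 30-35 reproductive years (assumption), using 4.2 to 4.5 births: from 2 × 4.2/35 = 0.24 to 2 × 4.5/30 = 0.30.

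**3. Cut needed for each row** (difference divided by the assumed control rate).

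| Difference | Rate 0.25 | Rate 0.35 | Rate 0.50 |
|---|---|---|---|
| 1.0 | 400% | 286% | 200% |
| 0.5 | 200% | 143% | 100% |
| 0.3 | 120% | 86% | 60% |
| 0.2 | 80% | 57% | 40% |

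At the extreme rate of 0.53, the 0.5 row needs 0.5/0.53 = 94%.

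**4. What the stated metric can detect.** With SD 2, the difference detectable with 80% power is (1.645 + 0.842) × 0.1047 = 0.26 one-sided and (1.960 + 0.842) × 0.1047 = 0.29 two-sided. That is about the whole number of births expected at the spread-out rates in step 2.

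**5. Coherence with the contraceptive calculation.** If 6.5 points of additional use are to give 0.5 fewer births, each additional user must avert 0.5/0.065 = 7.7 births in 2 years. The 0.2 row needs 0.2/0.065 = 3.1.

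**6. A scale that fits the follow-up.** Take the outcome as any birth or pregnancy conceived after randomisation, with assumed control risk p₁ of 20-40%. Solve p₁ − p₂ = (z + 0.842) × √[(p₁(1−p₁) + p₂(1−p₂))/n]. Check at 20%, n = 730, one-sided: p₂ = 0.1506, and 2.487 × √[(0.1600 + 0.1279)/730] = 0.049.

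| n per arm | One-sided, 80% power | Two-sided, 80% power |
|---|---|---|
| 730 | 4.9-6.3 points | 5.5-7 points |
| 834 (1669 retained, equal split assumed) | 4.6-5.9 points | 5.2-6.6 points |

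**7. Percentage.** 0.5/4.5 = 11.1%, not 12%.

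**The case against.** The strongest defence is that nothing is miscalculated: Table 4 is right for its inputs under the test the plan specifies. That stands, so the fault is in the planning assumptions and not in the power arithmetic.

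A reader might infer more than the documents support, in four ways.
- *Every row of Table 4 is unattainable.* This is not shown. At 0.50 births in 2 years the 0.3 row needs a 60% cut and the 0.2 row a 40% cut. A population-average rate is also not a strict ceiling for married women selected as pregnant or recently delivered.
- *The trial is underpowered for fertility.* This does not follow. On births since randomisation the SD is far below 2, and power for a 6.5-point reduction at 730 per arm is about 83-95% one-sided for control risks of 40% down to 20%. The Analysis Plan's model also includes the baseline outcome, which would remove much of the variation in prior children.
- *A 6.5-point rise in use caps the effect at 0.065 births.* The 6.5 points is a detectable difference, not a forecast or a maximum. Method mix and continuation, both listed as outcomes, could change births without changing end-line prevalence. The 7.7 figure is therefore a benchmark for coherence.
- *The protocol ignored its short follow-up.* It did not. It halved the effect partly for that reason, but not by enough.

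The article also never calls 4.5 a lifetime figure. That is inferred from its DHS source and from Study Setting, which treats the total fertility rate as average births per woman ("the total fertility rate or the average number of births per woman has remained relatively high in Malawi") and reports that "the average total fertility rate in Malawi was 4.2 births per woman". The objection to the 0.5 difference remains whatever 4.5 is called, because only births after randomisation can separate the arms.

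**Conclusion.** The point holds in a limited form. The 99% is correct arithmetic on an effect that the design could hardly produce. On rates derived from the protocol's own 4.5, the 1.0 row is impossible and the 0.5 row needs virtually no later births in the intervention arm. The 0.3 row needs 60-120% of control births averted and the 0.2 row 40-80%, the latter implausible but not impossible. The effects also sit poorly with the planned 6.5-point change in contraceptive use. The 2-year birth rates and the 20-40% control risks are assumptions, because the article states neither. Fieldwork is complete, so what changes is how the fertility result is read and not the design. It still needs correcting, because this is the power statement for the outcome that was primarily powered. The 12% is a minor slip.

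**What to change.** Withdraw the 99% claim and replace Table 4. State power for a birth or pregnancy conceived after randomisation, by the year-2 survey. Give the assumed control risk with its source, or a 20-40% range, and the plan's one-sided alpha of .05, with two-sided figures alongside if wanted. Report detectable differences for 730 per arm and for the 1669 women retained, using the actual split by arm in place of the equal split assumed here. Say how the chosen effect relates to the 6.5-point contraceptive effect. Change 12% to 11%.

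The cost is one paragraph and one table, with no new data. The downside is that the stated power becomes less favourable than 99%.
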